## Abstract

**Background:**

Multiple international agencies, including the World Health Organization and the International Monetary Fund, have emphasized the importance of maternal mental health for optimal child health and development. Adequate social support is vital for the most vulnerable to postpartum mood disorders. Hence, an urgent need for sustainable social support programs to aid mothers ease into their new parenting role exists.

**Objective:**

This study protocol aims to examine the effectiveness of a technology-based peer support intervention program among mothers at risk for postnatal depression in the early postpartum period.

**Methods:**

A randomized controlled 2-group pretest and repeated posttest experimental design will be used. The study will recruit 118 mothers from the postnatal wards of a tertiary public hospital in Singapore. Eligible mothers will be randomly allocated to receive either the peer support intervention program or routine perinatal care from the hospital. Peer volunteers will be mothers who have experienced self-reported depression and will be receiving face-to-face training to support new mothers at risk of depression. Outcome measures include postnatal depression, anxiety, loneliness, and social support. Data will be collected at immediate postnatal period (day of discharge from the hospital), at fourth week and twelfth week post childbirth.

**Results:**

The recruitment and training of peer support volunteers (N=20) ended in June 2017, whereas recruitment of study participants commenced in July 2017 and is still ongoing. The current recruitment for new mothers stands at 73, with 36 in the control group and 37 in the intervention group. Data collection is projected to be completed by May 2018.

**Conclusions:**

This study will identify a potentially effective and clinically useful method to prevent postnatal depression in new mothers, which is the top cause of maternal morbidity. Receiving social support from others who share similar experiences may enhance the positive parenting experiences of mothers, which in turn can improve the psychosocial well-being of the mothers, tighten mother-child bond, and enhance overall family dynamics for mothers and infants.

**Trial Registration:**

International Standard Randomized Controlled Trial Number ISRCTN14864807; http://www.isrctn.com/ISRCTN14864807 (Archived by WebCite at http://www.webcitation.org/6xtBNvBTX)

## Introduction

The mental well-being of women is highly vulnerable after childbirth, with postpartum mood disorders being the top cause of maternal morbidity [1,2]. The severity of these postnatal affective disorders can range from early maternity blues [3] to postpartum psychosis, which affects less than 1% of mothers [4,5]. Among these affective disorders, postnatal depression (PND) is the most common [5]. Women who have suffered PND often report feelings of inadequacy [6-8], disconnection from others [9,10], role conflicts [8,9,11], loneliness [9], anxiety [11-13], dissatisfaction with life [6,14], insomnia [14], and for severe cases, suicidal ideation [10,15]. Women are susceptible to PND in the first 12 weeks postpartum [16], with the duration dependent on severity [17] and time to onset of the treatment [18]. A total of 50% of clinically depressed mothers have experienced PND symptoms for at least 6 months postpartum [19,20], whereas approximately 25% of untreated mothers experience the symptoms for at least a year [21].

PND poses a huge mental health threat for women, with recent literature reporting an estimated prevalence rate of 10% to 15% for major PND [22,23]. Despite the insufficient statistics in the Singapore context, a recent local study by Shorey et al has discovered that the prevalence of PND symptoms at 4 weeks post birth is at 13% [24]. Additionally, the national G *rowing up in Singapore Towards Health Outcomes* (GUSTO) study [25] has revealed that across the general population, the increased maternal emotional difficulty during pregnancy has adverse effects on child neurodevelopment, in particular, brain regions associated with cognitive and emotional function. These results are supported by other studies that have examined how PND affects the quality of mother-child interactions [26] and has a significant adverse effect on the development of a child [13]. Mothers suffering from PND tend to be more hostile toward the infant [27,28], display disengaged parenting behaviors [27], and are unresponsive toward their infants’ cries [29]. These tendencies increase the risk of attachment anxiety, social behavioral problems [28], and psychopathology [30] in the affected child. Therefore, curbing the risk for depression and anxiety is necessary not only at an individual level but also for the general public health and societal capacity.

### Causes of Postnatal Depression

To date, the causes of PND remain uncertain, with considerable amount of literature suggesting a multifactorial etiology [3,9,31]. However, many studies can identify the primary risk factors for PND. Apart from a history of psychopathology [9,32,33] and demographic variables, such as young age [3], single marital status [32], and low socioeconomic status [3,32], psychosocial variables, such as insufficient social support [14,34], low maternal self-esteem [11,32], marital conflict [14,35], life stress [11,33,34], and childcare stress [9,22,32], are also major predictive factors of PND. The detailed analysis of predictive studies has further revealed underlying issues commonly faced by mothers, which can increase the risk of PND. Common social deficiencies experienced by mothers include insufficient initiated support by others [3,7,22,33], the lack of a close friend to confide in [9], and the inability to find a nonjudgmental person that can listen and empathize with them [36,37].

### Prevention of Postnatal Depression

In previous studies [6,7,14,36,38], emotional and instrumental support have been shown to be important in preventing PND. A previous study has revealed that instrumental support is preferred by mothers more than emotional support [7]. In a study by Gebuza [39], relationship between perceived instrumental support and actual support provided have also been found to be significant, as compared with emotional and informational support. Moreover, the mean social support received from significant others has helped mitigate the decline in mothers’ quality of life after childbirth [39]. Social support through companionship from significant others [6,14,36,38] and family members [3,36,38,40], as well as group belongingness with other identical individuals [36], have also been shown to serve as a protective barrier against PND. Alternatively, in the study of Leahy-Warren et al, no protective relationship was observed between professional support and PND [38]. In addition to social support from family and significant others, the study of Dennis et al also revealed the importance of support from other experienced mothers [36]. New mothers who share experiences with other mothers feel a sense of belonging and reassurance [6,10], which has helped boost their confidence in child rearing and reduced negative feelings [36]. The results from this study suggest that simple intervention means, such as talking to an experienced mother with similar stressors or situation, can act as a buffer against PND [6,10,41].

In addition, numerous randomized controlled trials [42-45] have been conducted to evaluate the effectiveness of psychosocial support interventions to prevent PND. These trial interventions are mostly conducted immediately after post birth [46,47] and primarily targeted high-risk women in professionally led antenatal groups [48,49]. Methodological limitations for these trials include poor measurement of PND and premature timing of outcome assessment. In a large scale Australian trial [47], postoperation debriefing by midwives are not only found ineffective in improving the psychological well-being of mothers but also has actually worsened the emotional health of mothers at 24 weeks. A local trial [50], which evaluated the success of a postpartum psychoeducational program, also found a significant effect in reducing PND. This intervention is administered by midwives paying home visits; therefore, the sustainability of this program is limited by the scarcity of midwives.

### Gaps in the Literature

The scarcity of resources and advancement of technology has led to an increasing trend in telemedicine, which is a previously underutilized platform in the health care sector [51-55]. Technology-based interventions are not only accessible and cost-effective; they also enhance privacy, flexibility, and reduce stigmatization [56,57]. These interventions are especially important for a multiracial, conservative society, such as Singapore, where traditional views and homebound confinement practices restrict new mothers from seeking the necessary help after childbirth [58,59]. Therefore, technology-based support will be the most practical alternative form of support for local mothers. Previous studies have successfully implemented technology-based support intervention for new mothers [51,60]. Technology-based peer support has effectively helped mothers maintain breastfeeding for 3 months postpartum as compared with those in the control group [60]. In another technology-based peer support study [51], pregnant mothers who received support were shown to have decreased anxiety and depressive traits. The risk of PND was also reduced to half of those in the control group. From these studies, we can deduce that the use of technology-based support may be effective in reducing the risk of depression for high-risk mothers.

The aim of this study is to examine the effectiveness of a technology-based peer support intervention program among mothers at risk for postnatal depression in the early postpartum period. This study has 3 objectives:

To evaluate the peer support intervention program on maternal outcomes, including PND (primary outcome), anxiety, loneliness, and social support (secondary outcomes)To analyze mothers’ evaluations of their peer support experienceTo analyze peer volunteers’ evaluations of their peer support experience

We hypothesized that when compared with those in the control group receiving routine care, mothers receiving the peer support intervention program will report a significantly lower level of PND, lower level of anxiety, lower level of loneliness, and higher level of social support received.

## Methods

### Design

A randomized controlled, single-blinded, 2-group pretest and repeated posttest experimental design will be used. Mothers (n=118) recruited from the postnatal wards of a tertiary public hospital will be randomly allocated to 2 groups (intervention group receiving the peer support intervention program and routine perinatal care from the hospital or control group receiving only routine perinatal care from the hospital). Data will be collected at immediate postnatal period (on day of discharge from the hospital), at the fourth week, and the twelfth week post childbirth using Web-based questionnaire surveys that include locally validated and reliable instruments, semistructured face-to-face interviews, and telephone interviews.

### Participants

Potential participants must be mothers who (1) are at least 21 years old, (2) can speak and read English, (3) own a telephone and are willing to share their number, and (4) plan to stay in Singapore for the first 3 months post childbirth. The inclusion criteria for the peer volunteers are mothers who (1) are at least 21 years old, (2) can speak and read English, (3) have delivered healthy baby in the past, (4) have self-reported history of and recovery from PND, (5) have a phone and are willing to share their number and call needy mothers as instructed by the research team, and (6) plan to stay in Singapore for next 6 months from the time of recruitment to participate in the mother-to-mother peer support intervention program. The exclusion criteria for the participants are mothers who (1) have a history or existing psychiatric illnesses, cognitive impairment, “and” or “or” major medical conditions that can interfere with their ability to participate in the study, (2) have had a vacuum- or forceps-assisted delivery with fourth-degree perineal tear; and/or (3) has given birth to a stillborn or a newborn with birth defects and/or medical complications. The exclusion criteria for the peer volunteers are as follows: (1) they have any physical or mental disorders that can interfere with their ability to participate in the study and (2) do not want to share their number and call needy mothers as instructed by the research team.

**Figure 1 figure1:**
[figure not shown]
Peer Voluntary Activity Log. Overall rating: 1 least satisfied; 5 most satisfied.

### Sample Size Determination

Psychosocial and educational interventions in perinatal period often result in a medium to large effect size on outcome variables [62], such as parenting self-efficacy [24]. Therefore, we can reasonably regard the peer support intervention to have a medium-size effect on the outcome variables. In our study, a 2 sample *t* test will be used to test for differences between the 2 groups. The required sample size to detect a medium effect size of 0.6 (*t* test) at a power of 80% and a significance level of 5% (2-sided) is 45 in each group [63]. In addition, when considering the dropout rate of 30% based on a previous similar study [62] and a preliminary study [24], a minimum sample size of 118 (45×2+45×2×30%=90+28=118) participants, with 59 in each group, is required for this study.

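### The 30% dropout allowance is added to the completers needed instead of divided out, so 118 mothers give about 77% power, not 80%, if 30% are lost

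*Protocol article*

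**What the plan says.** All of the calculation is in the protocol article, Methods, Sample Size Determination. The test is named there: "a 2 sample *t* test will be used to test for differences between the 2 groups". The target follows: "The required sample size to detect a medium effect size of 0.6" by t test, "at a power of 80% and a significance level of 5% (2-sided) is 45 in each group". The allowance for loss is introduced with "when considering the dropout rate of 30% based on a previous similar study" and a preliminary study, and the total is "a minimum sample size of 118 (45×2+45×2×30%=90+28=118) participants, with 59 in each group, is required for this study".

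The figure of 118 returns in the Abstract, the Design section and the Randomization section. In the last, mothers draw a number from 1 to 118, and a generated set of 59 numbers defines the intervention group.

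The Data Analysis section adds two relevant facts. Missing data are to be replaced for the intention-to-treat analysis, with a per-protocol analysis alongside. The intervention effect is to be tested by ANCOVA, with age and education level given as example covariates.

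**The concern.** The printed formula multiplies the completers needed by 1.30. A dropout rate is ordinarily a share of those enrolled, and the article does not define it otherwise. Taking 30% away from 118 does not return 90, so the paragraph does not meet its own requirement under its own assumption.

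What is at stake is the stated power. It is meant to show that the trial can detect an effect of 0.6 with 80% probability after the expected losses. If those losses occur, the probability is lower, and anyone weighing a null 12-week result against 80% power would give it slightly too much weight.

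**Working it through.** **Inputs**, all from Sample Size Determination: two-sample t test, standardized effect d = 0.6, power 80%, two-sided 5%, 45 per group (90 in total), dropout 30%, total 118 (59 per group).

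**1. The base figure reproduces.** Solving the noncentral t for d = 0.6, 80% power and two-sided 5% gives n = 44.6, so 45 per group. Power at 45 per group is 80.4%. The normal approximation gives 44. The base is sound.

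**2. The printed total reproduces only with the 1.30 multiplier.**
- Multiplying: 45 × 1.30 = 58.5, rounded up to 59 per group, and 2 × 59 = 118. This matches.
- Dividing: 45 / 0.70 = 64.3, rounded up to 65 per group, and 2 × 65 = 130. Rounding only the total gives 90 / 0.70 = 128.6, so 129. Neither matches.

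**3. What 118 leaves after 30% loss.** 118 × 0.70 = 82.6 completers, or 59 × 0.70 = 41.3 per group, against the 45 required.

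**4. Power at that size** (d = 0.6, two-sided 5%):

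| Completers per group | t test | Normal approximation |
|---|---|---|
| 41 | 76.5% | 77.5% |
| 41.3 | 76.9% | 77.8% |
| 45 (target) | 80.4% | 81.2% |

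The gap to the stated 80% is 80 − 76.9 = 3.1 to 80 − 76.5 = 3.5 points by t test, and 2.2 to 2.5 points by the normal approximation.

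**5. Detectable effect.** At 80% power the t test detects d = 0.624 with 41.3 per group and d = 0.626 with 41, instead of 0.60.

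**6. The dropout that 118 can absorb.** Completers stay at 90 or more up to 1 − 90/118 = 23.7%. Power itself reaches exactly 80% at 44.6 per group, which is 1 − 44.6/59 = 24.4% dropout. Both round to about 24%.

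**7. Check of the divided figure.** With 65 per group and 30% loss, 65 × 0.70 = 45.5 per group remain and t-test power is 80.8%.

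**8. What baseline adjustment might recover.** Adjusting for a baseline score that has correlation r with the 12-week score acts approximately like a standardized effect of 0.6/√(1 − r²). The documents give no r, so the values below are assumptions. They apply to 41 per group.

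| Assumed r | Effective d | Power |
|---|---|---|
| 0.1 | 0.603 | 77.0% |
| 0.2 | 0.612 | 78.2% |
| 0.3 | 0.629 | 80.3% |
| 0.4 | 0.655 | 83.4% |
| 0.5 | 0.693 | 87.3% |

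**The case against.** The strongest reply is that little is lost. The effect of 0.6 is a judgement, and a move to about 0.62 or 0.63 is well within its uncertainty. The slip does not bias the estimate, inflate the type I error or change the allocation, and at 24% dropout or less the stated power holds. All of this stands, and it limits the severity of the point.

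A second reply is that the planned analysis makes up the loss, because missing data are replaced and ANCOVA is used. This stands only in part. Replacing missing values does not supply the information of observed outcomes, and a calculation that adds a dropout allowance is already sized on completers. ANCOVA can gain power, but the section bases the size on an unadjusted t test, and the example covariates in Data Analysis do not include baseline EPDS.

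Two stronger readings are tempting. A reader might count a second arithmetic error, since 30% of 90 is 27 and the article prints 28. The simpler explanation is whole-number rounding of 58.5 to 59 per group, which the article uses throughout and which adds one mother. It is not a separate error. A reader might also infer that the trial is seriously underpowered. A shortfall of 3 to 4 points, conditional on 30% loss, does not support that.

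**Conclusion.** The allowance is wrong as printed. Under the plan's own 30% dropout, 118 mothers yield about 41 completers per group and about 77% power by t test at d = 0.6, not 80%. The total is 129 − 118 = 11 short, or 130 − 118 = 12 short with equal groups. This should be fixed, but it does not undermine the trial.

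The conclusion rests on reading the 30% as a share of mothers enrolled, which nothing in the article contradicts, and on equal loss in the two groups. It also keeps the article's own test and effect size.

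It would go too far to say that baseline adjustment restores 80%. Of the correlations tabulated, 0.3 is the lowest that does so, and the documents give no value. Entry is limited to an EPDS score of at least 9 (Study Procedure), which narrows the baseline range and may lower the correlation.

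**What to change.** Keep 118 and correct the statement in Sample Size Determination. It should say that with 30% dropout about 41 mothers per group complete, which gives about 77% power for d = 0.6 by t test, and that 80% is kept only if dropout is no more than about 24%. This changes wording only. It adds no mothers and leaves the 118-number randomization as it is. The cost is a slightly less favourable stated power.

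Optionally, name baseline EPDS as a covariate in the ANCOVA already planned in Data Analysis. That is an analysis decision and not just a rewording. If power is quoted for it, show the range over the assumed correlations (77.0% to 87.3% for r from 0.1 to 0.5) and do not promise a return to 80%.

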### Randomization

After confirming the eligibility criteria and obtaining the consent of the participants, all mothers will be randomized into 2 groups. Mothers who give consent to participate will be asked to choose a number from 1 to 118 from an opaque envelope. The research randomizer [64] will be used to generate 1 set of 59 numbers. Participants whose picked number matches with any number in the set will be assigned to the intervention group (PIP intervention), and the remaining will be assigned to the control group. The principal investigator, who is not involved in recruitment, intervention, and data collection, will generate the random numbers and will pass them to RA1, who is not involved in data collection.

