For phase 2, ethics approval has been granted (NHG DSRB: 2017/00815), and participant recruitment has commenced in the postnatal clinics at the study venue. RA1 has informed the nurse managers and clinicians of the respective postnatal wards of the study. The nurse in charge creates a short list of eligible participants based on the selection criteria and verifies the overall physical and psychological well-being of the women. RA1 then approaches those women who meet the inclusion criteria and explains the study purpose and details to them. Voluntary participation is emphasized. Those who are keen to participate are screened using EPDS. On the basis of previous studies [60,61], only mothers with an EPDS score of at least 9 are recruited. After RA1 obtains their written consent, the participants are randomized and grouped into the intervention or control groups accordingly. Participants are then asked to fill a baseline questionnaire, a demographics form, as well as to provide their name and contact information for future data collection and correspondence purposes.

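### Concealment is inadequately protected: the assistant who approaches and consents mothers also holds the set of intervention numbers

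*Protocol article*

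**What the plan says.** The Randomization section describes a pool of 118 numbers, 59 of which denote the intervention. The draw comes after eligibility and consent: "Mothers who give consent to participate will be asked to choose a number from 1 to 118 from an opaque envelope". A mother whose number is in the set of 59 goes to the intervention group, and the others go to control. The principal investigator, who is described as outside recruitment, intervention and data collection, "will generate the random numbers and will pass them to RA1, who is not involved in data collection".

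Study Procedure gives RA1 the recruiting role. The preliminary list is not RA1's: "The nurse in charge creates a short list of eligible participants based on the selection criteria". After that, "RA1 then approaches those women who meet the inclusion criteria and explains the study purpose and details to them". On screening the text names nobody: "Those who are keen to participate are screened using EPDS". It continues: "After RA1 obtains their written consent, the participants are randomized and grouped into the intervention or control groups accordingly". The baseline questionnaire and demographics form come after that step.

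The section on components of the intervention has RA1 match each intervention mother to a volunteer, using availability and demographics, mode of delivery in particular. Data Collection assigns outcome measurement to RA2, who takes no part in randomization or the intervention.

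**The concern.** Concealment requires that the person who decides whether a mother enters, and who handles the step that fixes her arm, cannot act on knowledge of that arm before it is irrevocably recorded. Keeping the principal investigator out of recruitment serves that aim only while the principal investigator alone holds the key. Here the key goes to the recruiter, so the separation is lost at the point where it matters. The reason given for trusting RA1 with it, no role in data collection, guards against biased outcome assessment. It does nothing for allocation.

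The envelope hides the number from the mother and from RA1 until it is drawn. It does not hide what the number means once it is out. Between the draw and the record, RA1 alone knows the result. An unrecorded second draw, or the quiet loss of a consented mother, could then follow from knowing her arm. Either would make the groups differ for reasons other than chance, and no analysis of the recorded data could detect or correct it. At stake is whether the report can describe allocation as adequately concealed.

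**Working it through.** **1. Roles side by side**

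| Step | Who | Section |
|---|---|---|
| Generates the 59 numbers | Principal investigator | Randomization |
| Receives the 59 numbers | RA1 | Randomization |
| Short-lists eligible women | Nurse in charge | Study Procedure |
| Approaches and explains the study | RA1 | Study Procedure |
| EPDS screen | Not named | Study Procedure |
| Obtains written consent | RA1 | Study Procedure |
| Draws the number | The mother | Randomization |
| Pairs intervention mothers with volunteers | RA1 | Components of the intervention program |
| Collects outcomes | RA2 | Data Collection |

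One person recruits, consents and can decode the draw.

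**2. What RA1 knows, and when**

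The order is eligibility, consent, draw, arm, baseline. The 59 numbers are an unordered code, not a sequence of coming assignments. At approach and at consent, RA1 does not know which number the mother will draw. At the draw, RA1 knows the arm at once. Exposure therefore begins at the draw and ends when the arm is recorded. Because baseline comes later still, a mother lost in that interval may have no baseline record.

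**3. The plan's own figures**

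- Pool: 59 + 59 = 118, as stated.
- Enrolled: 37 + 36 = 73, as stated in Results.
- Remaining: 118 − 73 = 45.
- If drawn numbers are not returned, the remainder is 59 − 37 = 22 intervention and 59 − 36 = 23 control numbers.

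The sample size behind the pool also reproduces: an effect size of 0.6, 80% power and two-sided 5% give 44.6, rounded up to the stated 45 per group. It has no bearing on this point.

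**4. What one unrecorded redraw would do**

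Assume that RA1 wants a given arm for a given mother and that exactly one redraw goes unrecorded. Then P(wanted arm) = 1 − P(first draw unwanted) × P(second draw unwanted).

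At the start of recruitment:
- No redraw: 59/118 = 50%.
- Redraw, first number put back: 1 − 0.5 × 0.5 = 75.0%.
- Redraw, first number set aside: 1 − (59/118) × (58/117) = 1 − 0.248 = 75.2%.

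At the reported 73, with 22 intervention and 23 control numbers left:
- Intervention wanted: 22/45 = 48.9% without a redraw. With one it is 1 − (23/45)² = 73.9% if the number is put back, or 1 − (23/45) × (22/44) = 74.4% if it is set aside.
- Control wanted: 23/45 = 51.1% without a redraw. With one it is 1 − (22/45)² = 76.1% or 1 − (22/45) × (21/44) = 76.7%.

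The result is about 75% throughout (range 74% to 77%), whether or not numbers are returned.

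**The case against.** **The blind draw.** The strongest defence is the order of events. Eligibility and consent come before the draw, and the set of 59 says nothing about the next mother until she has picked a number. This stands. A reader might infer that allocation is not concealed at all, or that RA1 can choose whom to approach by arm. The documents do not support that. RA1 cannot delay or decline an approach in response to a number that has not yet been drawn.

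**Screening.** A reader might also infer that RA1 administers the screening EPDS. The sentence is passive and names no one, and a nurse makes the short list. The point does not need that inference.

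**Guessing from the remaining mix.** One could try to size the problem by how well RA1 could predict the next arm from the numbers left. That predictability comes from the fixed 59/59 split, assumes that drawn numbers are not returned (the text does not say), and would persist under any remedy in which RA1 learns each arm afterwards. It does not measure this defect.

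**Misconduct and traces.** What remains requires a deliberate act. The mother herself draws, and a dropped enrolment leaves a signed consent form. This is fair: the route is narrow and not wholly invisible. Even so, a mother need not know that a second draw is improper, and a consent form without an arm does not show why she left.

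**Motive.** Volunteer availability gives RA1 a conceivable reason to prefer one arm on a given day, but no shortage is shown. With even accrual over a year and four weeks of support, 59 intervention mothers occupy about 59 × 4/52 = 4.5 of the 20 volunteers at once. With twelve weeks it is 59 × 12/52 = 13.6. Matching on mode of delivery could tighten this, by an amount the article does not give.

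**A condensed article.** Who supervises the envelope, logs draws and bars redraws may be in the full protocol, and its absence here is not held against the plan. Passing the key to the recruiter is different, because the article states it as the procedure.

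**Conclusion.** The concern holds in a limited form: concealment is inadequately protected, but not absent. The stated procedure gives the recruiter the key, so the arm can be read between the draw and its recording. The surviving routes to bias are an unrecorded redraw and the loss of a consented mother after the draw. A permitted redraw moves the chance of a wanted arm from 50% to about 75% for that mother. This assumes a single redraw and a recruiter who wants a particular arm.

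The documents give no basis for saying how often this could occur or how far it would shift the EPDS comparison, so no bias in outcome units is claimed. The reported 37/36 split neither suggests nor excludes manipulation. The point merits correction because the remedy is cheap and a large part of recruitment was still open.

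**What to change.** For the 45 enrolments remaining at the reported count:

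- The principal investigator, already outside recruitment, keeps the set of intervention numbers.
- Consent and baseline are completed first, and then the mother draws.
- RA1 sends the participant ID and the drawn number. Both are logged in sequence with the time, and no redraw is accepted.
- Only then is the arm returned to RA1 for pairing with a volunteer.

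Since RA1 will by now have had the present set, withholding it is not enough by itself. The principal investigator should reassign at random which of the unused numbers denote the intervention. If drawn numbers have been removed, that is 22 of 45, which preserves 59 per arm.

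The report should state that the mothers enrolled before the change were allocated with the key held by the recruiter. It should also reconcile signed consents against recorded allocations for all mothers.

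The cost is one message per enrolment and no new staff, and the sample size does not change. The practical burden is timing. Baseline is set for the day of discharge, so the key-holder must be reachable then for the arm to be returned without delaying the planned first volunteer contact. If the full protocol already has the key held elsewhere, correcting the sentence in the Randomization section is enough.
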